### Stage II: follow-up period after discharge from the NICU

Develop a follow-up observation table for preterm children <34 weeks, and require the children’s health care medical staff to record the data of follow-up every time in detail.Require the preterm children to revisit the hospital’s Child Health Clinic for referral 2 weeks, 4 weeks and 3 months after discharge, and follow up once every 2–4 weeks according to the preterm children’s conditions 4 weeks later.Call the children’s parents 1–2 day before every referral and require them to bring the children to our hospital for referral on time, and ask them to bring all medical data.Contents of referral at the Child Health Clinic include measurement of physical growth and development, assessment of neuropsychological development, nutritional assessment and feeding guidance. According to different conditions of the preterm children during hospital stay, choose whether to conduct blood, liver function, thyroid function, head B-mode ultrasound or cranial magnetic resonance imaging (MRI), retinopathy (ROP) screening, hearing screening and other tests.Explain the current follow-up results in detail to the parents, and appoint the time and contents of next follow-up.Call the parents again on the night or the next day of follow-up every time to inquire about follow-up conditions in detail, and again record all follow-up results.Follow-up period: at least 3 months.

### Data collection and management

Including the collection of clinical data of preterm children during the NICU stay and follow-up data after discharge from the NICU.

### Collection of clinical data during the NICU stay

Collection of general data of the objects of study:Sex, gestational age, birth weight, birth head circumference, birth body length, mode of delivery, 5-minute Apgar score, etc., of preterm childrenMother’s pregnancy complications and comorbidities: premature rupture of membrane >24 hours, placental abruption, chorioamnionitis, pregnancy-induced hypertension syndrome, preeclampsia, gestational diabetes, hyperthyroidism, hypothyroidism, systemic lupus erythematosus, kidney disease, cholestasis, acute liver failure, syphilis infection, etc.Special treatment: nasal continuous positive airway pressure (nCPAP), intubation and mechanical ventilation (MV), use of pulmonary surfactant (PS), thoracentesis, bone marrow biopsy, thoracic drainage, peritoneal dialysis, etc.Collection of case data during the NICU stay:

Incidence and outcome of feeding intolerance in preterm children, neonatal necrotizing enterocolitis, cholestasis, parenteral nutrition-associated cholestasis and congenital hypothyroidism3.Collection of enteral and parenteral nutrition and defecation conditions during the NICU stay:Milk opening time (h), total amount of daily milk (ml) and calories (kcal), total amount of daily parenteral nutrition (ml) and calories (kcal), total volume of daily fluids (ml) and total calories (kcal)The number of daily bowel movements, times of daily enema, trait and color of stool every time, meconium drainage time (h)Gastric residual volume (ml) and nature, times and nature of vomiting, and abdominal distensionTime to achieve full enteral nutrition (d), and total time of parenteral nutrition4.Collection of physical growth and development indicators during the NICU stay:Weight: weight will be measured at admission, once every day during hospital stay and before discharge with a baby electronic scale, and the data will be accurate to 10 g.Body length: body length will be measured at admission, once every week during hospital stay and before discharge, and the data will be accurate to 0.1 cm.Head circumference: head circumference will be measured at admission, once every week during hospital stay and before discharge, and the data will be accurate to 0.1 cm.5.Collection of laboratory indicators during the NICU stay:Daily monitoring of peripheral blood glucose and transcutaneous bilirubinWeekly detection of blood, liver and kidney function (total protein, albumin, total bilirubin, direct bilirubin, alkaline phosphatase, bile acids, alanine aminotransferase, aspartate aminotransferase, γ-glutamyl transferase, urea nitrogen, creatinine) and electrolytes (mainly calcium and phosphorus)Test of serum thyroid function 1–2 weeks after admission, including TSH, TT_3_, TT_4_, FT_3_ and FT_4_

### Collection of follow-up data after discharge from the NICU

Weight: weight will be measured once 2 weeks, 4 weeks and 3 months after discharge, respectively, and the data will be accurate to 10 g.Body length: body length will be measured once 2 weeks, 4 weeks and 3 months after discharge, respectively, and the data will be accurate to 0.1 cm.Head circumference: head circumference will be measured once 2 weeks, 4 weeks and 3 months after discharge, respectively, and the data will be accurate to 0.1 cm.

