
In China, preterm children with a gestational age of less than 34 weeks are mostly fed with preterm children’s formula, and such milk powder provides sufficient energy, protein, vitamins and minerals and features a high growth rate in preterm children. However, excessive weight gain in early infancy will increase the risk of metabolic diseases and cardiovascular diseases in adulthood [21, 22]. The probabilities of feeding intolerance and neonatal necrotizing enterocolitis and overall mortality in preterm children fed with preterm children’s formula are significantly higher than in children fed with breast milk or donated breast milk [23–25]. Therefore, choosing a milk powder more suitable for the intestinal function of preterm children with a gestational age of less than 34 weeks is very important.

Hydrolyzed formula is to hydrolyze protein in milk powder to polypeptides, peptides and free amino acids with bio-lyase, heating, ultrafiltration and other special technologies. The American Academy of Pediatrics (AAP) refers to formula whose peptide molecular weight is less than 3000 Da as extensively hydrolyzed formula (EHF) [26]. According to the protein ingredient therein, the formula can be divided into hydrolyzed protein formula, hydrolyzed soy protein formula and hydrolyzed rice protein formula; according to the milk protein ingredient therein, the formula can be divided into hydrolyzed whey protein, hydrolyzed casein, and hydrolyzed whey protein/casein. The low-molecular-weight peptides and small amounts of free amino acids in extensively hydrolyzed milk protein formula have greatly reduced the conformation and sequence of allergen idiotope, and thus the antigenicity is greatly lowered. The milk powder is mainly used for the treatment of cow’s milk protein allergy (CMPA) [27]. Researchers have fed preterm children in their early stage of life with EHF to prevent the occurrence of CMPA [28, 29], but there is no conclusion on whether it is effective.

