### Study population

#### Recruitment of participants

Preterm children hospitalized in the NICU of Zhongda Hospital Southeast University in line with the inclusion criteria are recruited as participants (Fig. 1).

Inclusion criteria:Gestational age <34 weeksChildren who can only be fed with formula due to their mothers’ sicknessChildren who are transferred to our hospital’s NICU immediately after birth, and have not started any enteral feeding before and during transfer, including water, glucose, formula, drugs, etc.Children whose cardiovascular, blood and nervous systems are stable when transferred to the NICU

Exclusion criteria:Occurrence of vomiting, abdominal distension, gastrointestinal hemorrhage or necrotizing enterocolitis (NEC) before preparation for enteral feedingOccurrence of cardiovascular, blood and nervous system instability (such as shock, disseminated intravascular coagulation (DIS), frequent convulsions, coma) before preparation for enteral feedingDiscovery of gastrointestinal malformations (esophageal atresia, esophageal fistula, biliary atresia, Hirschsprung’s disease, anal atresia, omphalocele, gastroschisis, congenital malrotation, etc.) before preparation for enteral feeding or after feedingChildren with congenital metabolic diseases and chromosomal disordersChildren with other serious congenital disorders (diaphragmatic hernia, cyanotic congenital heart disease, moderate to severe Pierre-Robin syndrome, etc.)Renal failure due to various causesChildren whose head computed tomography (CT) or B-mode head ultrasound prompts serious intracranial hemorrhage or hydrocephalusUse of drugs affecting gastric motility and gastric acid secretion (H_2_ receptor antagonists, proton pump inhibitors, gastrointestinal drugs)Occurrence of stage III necrotizing enterocolitis during hospital stay requiring transfer to a Children’s Hospital for observation and surgical treatmentReplacement for formula during hospital stayDeath during hospital stayEarly discharge against the criteria for discharge from the NICUChildren who suffer from diseases requiring parenteral nutrition or serious illness requiring intensive care unit (ICU) hospitalization or requiring hospitalization and surgery

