#### Study design

The study includes two stages. In stage I, the study observes the incidence of feeding intolerance, parenteral nutrition conditions, spontaneous fecal discharge conditions, growth and development conditions and the incidence of other preterm children’s complications in the preterm children in the two groups during the NICU stay. In this stage, different feeding methods and parenteral nutrition are regulated according to the gestational age, birth weight and days after birth of the preterm children, and unified diagnostic criteria and treatment methods for different complications are developed. In stage II, the study follows up the growth and development conditions of the preterm children in the two groups on a regular basis after discharge from the NICU.

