### Stage I: NICU stay

Feeding timePreterm children without obvious high-risk factors are fed within 24 hours after birth.The feeding of preterm children with birth weight <1000 g, obvious history of asphyxia at birth (Apgar score ≤5), severe infection (sepsis, purulent meningitis, etc.), severe pneumonia or neonatal respiratory distress syndrome (NRDS) requiring intubation and mechanical ventilation should be postponed to 24–72 h after birth according to the situation.During the period when full enteral nutrition is not achieved, partial parenteral nutrition is given according to the daily amount of fluid and energy required by the children; when the children experience feeding intolerance and necrotizing enterocolitis and need to be fasting, complete parenteral nutrition is given; after the conditions are stable, the children gradually switch to enteral nutrition and are fed until discharge or transfer into DRI.Children in the two groups are fed with ordinary formula after discharge or transfer to DRI.Feeding methodsFor preterm children with a gestational age of <32 weeks, since their sucking-swallowing action is uncoordinated and respiratory function is not maturely developed, the children are given tube feeding (nasogastric tube or orogastric tube) using the intermittent infusion feeding method. Every time before feeding, the stomach contents are drawn to learn about gastric residual volume (GRV) and nature.Children suspected of suffering from gastroesophageal reflux or delayed gastric emptying are fed by adopting intermittent/continuous infusion feeding method with an infusion pump.Preterm children with a gestational age of 32–34 weeks are given direct bottle feeding.Children with weak sucking ability yet normal gastric emptying are given bottle feeding first, and then the remaining milk is given by tube feeding.Children with nasal continuous positive airway pressure (nCPAP) or intubation and mechanical ventilation are given tube feeding;During tube feeding or fasting period, the children are given non-nutritive sucking (NNS).Feeding milk volumeInitial feeding milk volume: according to birth weight, the children are fed from different initial milk volume once every two hours, as shown in Table 2.The milk volume begins to increase in the absence of feeding intolerance in 24-h observation, and the rates for milk increasing are shown in Table 2.

**Table 2 Tab2:** Initial feeding milk volume and increasing rate in the two groups of preterm children

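### Defined recording of intolerance, NEC and other complications ends when both arms change to ordinary formula, so the trial cannot compare gastrointestinal or serious events by arm after the change, and its safety conclusion reaches beyond its data

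*Protocol article*

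**What the plan says.** All references are to the protocol article.

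- **Scope of the stages (Study design).** Stage I covers intolerance, parenteral nutrition, stools, growth and "the incidence of other preterm children’s complications in the preterm children in the two groups during the NICU stay". The second stage is narrower: "In stage II, the study follows up the growth and development conditions of the preterm children in the two groups on a regular basis".
- **NICU data (Collection of clinical data during the NICU stay).** Under "Collection of case data during the NICU stay" stands "Incidence and outcome of feeding intolerance in preterm children, neonatal necrotizing enterocolitis, cholestasis, parenteral nutrition-associated cholestasis and congenital hypothyroidism". Daily residuals, vomiting, distension and stools are listed as well.
- **Post-discharge data (Collection of follow-up data after discharge from the NICU).** Three items are listed. The first is "Weight: weight will be measured once 2 weeks, 4 weeks and 3 months after discharge, respectively"; length and head circumference follow at the same times.
- **Formula change (Stage I: NICU stay).** "Children in the two groups are fed with ordinary formula after discharge or transfer to DRI".
- **Follow-up contacts (Stage II).** Visits fall at 2 weeks, 4 weeks and 3 months, with further visits as needed. They cover growth, neuropsychological development, nutrition and feeding advice, with optional blood, liver and thyroid tests. Parents are called around each visit and the results are recorded.
- **Exclusion (Recruitment of participants).** The last criterion covers diseases that need parenteral nutrition, and serious illness "requiring intensive care unit (ICU) hospitalization or requiring hospitalization and surgery". It has no time limit.
- **Intended conclusion (Discussion).** The results are expected to confirm that NICU feeding with this formula is safe and effective and leaves early growth unaffected.

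**The concern.** The case for the extensively hydrolysed formula (EHF) in the Background rests on hydrolysed protein, faster gastric emptying and reduced allergenicity ("and thus the antigenicity is greatly lowered"). The change to ordinary formula takes the EHF infants off that product. It falls exactly where defined event recording stops. Replacement of the formula during the hospital stay is itself an exclusion, so by plan no analysed EHF infant meets another formula while events are being counted.

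If gastrointestinal or serious events then differed between the arms, the listed data would not show it. A clinician adopting this formula adopts the whole sequence: EHF in the NICU, then ordinary formula. For the second part of that sequence the trial offers growth only. If the last exclusion criterion were applied after randomisation, even the growth data could lose the sickest infants.

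**Working it through.** **1. What is recorded on each side of the change**

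| | Up to discharge or DRI transfer | Afterwards |
|---|---|---|
| EHF arm (Table 1) | EHF, 1.6 g protein/100 ml, all whey | Ordinary formula, 1.4 g, protein form not stated |
| Control arm (Table 1) | Preterm formula, 2.6 g, 60 % whey and 40 % casein | The same ordinary formula |
| Intolerance, NEC, cholestasis, hypothyroidism | Listed, with diagnostic criteria | Not listed |
| Growth | Listed | Listed |
| Contacts | Inpatient charting | Visits and calls without an event list |

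The Outcomes section names NEC, cholestasis and hypothyroidism without a time window, but the Study design and data collection sections place them in the NICU stay. A DRI stay is covered by neither list: NICU collection has ended, and the follow-up visits are timed from discharge.

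**2. Is the primary endpoint affected?** No. The primary objective, the sample size section and the primary analysis all tie intolerance to the NICU stay. An infant without an event in that window is correctly event-free.

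**3. What the gap could hide (illustration only; the document gives no post-change rate)**

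Inputs from the sample size section are 85 % (control), 75 % (EHF) and 148 infants per group finishing the NICU part. The dropout step reproduces: 148 / (1 − 0.20) = 185. The 148 itself does not follow from 85 % against 75 % (about 250 per group, two-sided). That is a separate matter; 148 serves here only as a denominator.

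Let dE and dC be the assumed shares of NICU-event-free infants in the EHF and control arms who have a first event after the change. The cumulative difference is

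D = (0.85 + 0.15 dC) − (0.75 + 0.25 dE) = 0.10 + 0.15 dC − 0.25 dE.

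| dE | D if dC = 0 | D if dC = dE |
|---|---|---|
| 0 | 10.0 points | 10.0 points |
| 5 % | 8.75 | 9.5 |
| 10 % | 7.5 | 9.0 |
| 20 % | 5.0 | 8.0 |
| 30 % | 2.5 | 7.0 |
| 40 % | 0 | 6.0 |

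The EHF arm would have 148 × 0.25 = 37 event-free infants. Cancelling the planned difference would take 0.40 × 37 = 14.8, about 15 first events, with none among controls. The direction is open too: D exceeds 10 points whenever dC is more than 0.25 / 0.15 = 1.67 times dE.

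**4. The last exclusion criterion, read at three times**

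- *Before randomisation:* an ordinary eligibility rule.
- *In the NICU, after randomisation:* the Stage I section gives partial parenteral nutrition until full enteral feeding, and complete parenteral nutrition when intolerance or NEC requires fasting. Taken literally, the criterion could remove infants who have the very event being counted.
- *After discharge:* infants with later serious illness or surgery would leave the growth comparison.

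The text does not say which is meant. The criterion stands in a list with death, stage III NEC and formula replacement during the stay, all of which occur after randomisation.

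**The case against.** Several stronger readings are tempting, and the document does not support them.

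- **Postponed events are counted as prevented, biasing the result towards EHF.** The endpoint is openly a NICU-stay rate, and the different exposure inside that window is the randomised contrast, not a bias. No deferral rate is given. Both arms change formula, so setting control events to zero is the extreme case. Infants must also be at least 34 weeks corrected age and on full enteral feeds of at least 150 ml/kg a day before they leave, while the Background ties intolerance to gut immaturity below 34 weeks. Large deferral is therefore not obvious.
- **Follow-up is blind to events for 3 months.** Stage II keeps visits, a follow-up table, optional tests and calls with results recorded. An article may also leave form fields to the full protocol. What stands is that the article positively defines stage II as growth and development and attaches no event definition or endpoint to these contacts.
- **The trial asks whether the change is harmful.** The Abstract asks about growth and development, and the growth measures suit that question. The Discussion nevertheless goes further: it limits the feeding to the NICU stay but sets no time limit on the claim of safety.
- **EHF infants first meet intact protein at the change.** Table 1 does not give the protein form of the 0 to 6-month formula. Unhydrolysed protein is a reasonable inference from its description as ordinary, but it is an inference.
- **Readmitted infants are removed.** The last criterion mentions neither readmission nor discharge. It is ambiguous, and that ambiguity is the fault.

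**Conclusion.** The concern holds as a gap in the safety outcomes, not as an error in the primary endpoint. From discharge or DRI transfer, which is also when both arms change formula, no gastrointestinal or serious event is a defined outcome. The gap lasts for any DRI stay plus at least 3 months. The trial will therefore be unable to say whether such events differ by arm after the change, and a general statement of safety would go beyond its defined data.

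No bias can be quantified. The figures above rest on assumed event rates and show only that the answer depends on data the plan does not define. The last exclusion criterion is a related weakness: with no time limit it can be read as removing randomised infants because of illness, and it does not fit the parenteral nutrition described in the Stage I section. Overall this is a worthwhile, inexpensive improvement.

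**What to change.** 1. On the existing 2-week, 4-week and 3-month form and in the planned calls, record since the last contact: NEC, blood in stool, repeated vomiting, change of formula for intolerance, readmission, surgery and death. Cover any DRI stay.
2. Report these by arm as safety outcomes, with the post-change period shown separately from the NICU-stay primary endpoint, which stays as it is. Give them simple definitions of their own, since gastric residue and pre-feed girth are bedside measures.
3. If this is not done, limit tolerance and safety conclusions to the NICU stay.
4. Limit the last exclusion criterion to conditions present before randomisation. Keep infants who fall ill or are readmitted later in follow-up and analysis. Reconcile its parenteral nutrition wording with the Stage I section.

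The cost is a few lines on the form and in the call script. The contacts are already planned, and parents are already asked to bring all medical data. No treatment changes. The downside is that mild events reported by parents are less precise than NICU charting. In partial compensation, guardians are meant to be unaware of the assigned formula, whereas NICU staff are not. Enrolment began in November 2014, so infants who have already completed follow-up could be covered only from existing call and visit records.

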#### Secondary objective

To test if the feeding preterm children with a gestational age of less than 34 weeks during the NICU stay with extensively hydrolyzed milk protein formula can accelerate the time to achieve full enteral feeding, shorten the time of parenteral nutrition and NICU stay, benefit spontaneous fecal discharge, reduce the occurrence of other complications associated with parenteral nutrition, and meet the nutritional needs of preterm children during the NICU stay, without affecting the early growth and development of these preterm children during hospitalization and after discharge.

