### Study design and outcomes

#### Outcomes

The first endpoint variable is the rate of food intolerance in preterm children. The second endpoint variables include (1) time to achieve full enteral nutrition; (2) time of parenteral nutrition; (3) time of NICU stay; (4) meconium drainage time; (5) daily spontaneous fecal discharge conditions; (6) growth and development conditions during the NICU stay and within 3 months after discharge, including daily weight growth rate, weekly body length growth rate and weekly head circumference growth rate; (7) different plasma parameter indicators before discharge from the NICU (total protein (TP), albumin, calcium (Ca), phosphorus (P), and alkaline phosphatase (ALP)). Other endpoint variables include the incidences of neonatal necrotizing enterocolitis, cholestasis, parenteral nutrition-associated cholestasis and congenital hypothyroidism (CH).

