#### Secondary outcome

The time to reach enteral nutrition (parenteral nutrition), length of hospital stay, meconium drainage time during the NICU stay will be summarized and compared using Kaplan-Meier estimators and logrank tests. Cox models will also be fitted for time-to-event data adjusting for baseline covariates. The number of times of self-defecating per day will be compared using the Poisson model adjusting for baseline covariates. The rates of comorbidity will be compared using Poisson models. The plasma total protein, albumin level, calcium, alkaline phosphatase levels before discharge from the NICU will be compared using *t* tests. Growth rates measure by weight, body length, and head circumference during the NICU and within 3 months of discharge will be analyzed using repeated measurement analysis of covariance models. All analysis will be conducted using SAS 9.4 (SAS Institute, Cary, NC, USA).

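### Growth is measured in windows bounded by discharge, which the formula may shift and which itself depends on weight, so the growth-safety comparison is at risk of bias unless arms are also compared at a common corrected age

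*Protocol article*

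**What the plan says.** Under Outcomes, the sixth secondary endpoint is "growth and development conditions during the NICU stay and within 3 months after discharge, including daily weight growth rate", together with weekly length and head circumference rates. The section on follow-up data after discharge sets the schedule, "weight will be measured once 2 weeks, 4 weeks and 3 months after discharge, respectively", and repeats it for length and head circumference. Stage II counts clinic visits the same way: "2 weeks, 4 weeks and 3 months after discharge, and follow up once every". The statistical section on secondary outcomes says that growth rates "during the NICU and within 3 months of discharge will be analyzed using repeated measurement analysis of covariance models". It names no time scale or covariates for these models.

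The Secondary objective hopes the formula will "shorten the time of parenteral nutrition and NICU stay", and NICU stay is also a listed secondary endpoint. The same objective asks that this be achieved "without affecting the early growth and development of these preterm children during hospitalization and after discharge".

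The criteria for NICU discharge include corrected gestational age of at least 34 weeks, weight of at least 1500 g, full enteral feeding at 150 ml/kg or more daily, birth weight regained and steady gain. Under Interventions, both arms move to the same ordinary formula at discharge.

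**The concern.** The boundary between the two growth windows, and the origin for every post-discharge visit, is an event that treatment may move and that is partly defined by the outcome. No growth comparison at a common postnatal or corrected age is named. Three things can follow:

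- **NICU rates** are averaged over different lengths of stay, so the early days without net gain weigh differently in each arm.
- **Size at a visit** is compared at different ages. Earlier discharge makes an arm younger and smaller. An infant held back until the weight criterion is met is older at each visit, which conceals part of a deficit.
- **Post-discharge rates** are measured on the common formula. Catch-up then counts as better growth, and a size deficit already present at discharge drops out.

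At stake is whether a formula with 66 rather than 80 kcal and 1.6 rather than 2.6 g protein per 100 ml (Table 1) leaves early growth unaffected, a stated objective and a conclusion that the Discussion anticipates.

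**Working it through.** The plan has no figure of its own to reproduce here: it gives neither an expected difference in stay nor a growth margin. All sizes below are illustrations.

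**1. Attained size per day of shift.** The Background gives reference growth for the NICU stay: 15 g/kg/day, 1 cm/week length, 0.5–1 cm/week head circumference. Body weight of 1.5 kg is the discharge floor; 2.0 kg is assumed.
- Weight: 15 × 1.5 = 22.5 g per day; 15 × 2.0 = 30 g per day.
- Length: 1/7 = 0.14 cm per day.
- Head circumference: 0.5/7 to 1/7 = 0.07–0.14 cm per day.
- For assumed shifts of 3 and 7 days: 68 and 158 g at 1.5 kg; 90 and 210 g at 2.0 kg.

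These are offsets in size, not in rate.

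**2. NICU average rate.** Assume birth weight is regained on day 10 and gain is then 25 g/day, identically in both arms.
- 21-day stay: 25 × (21 − 10)/21 = 275/21 = 13.1 g/day.
- 24-day stay: 25 × (24 − 10)/24 = 350/24 = 14.6 g/day.

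Identical growth yields a difference of 1.5 g/day from length of stay alone.

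**3. Which way discharge might move.** The objective expects a shorter stay. The plan's figures also allow a push the other way. Full enteral nutrition is set at 100–120 kcal/kg/day. At 66 kcal/100 ml that is 100/0.66 to 120/0.66 = 152–182 ml/kg; at 80 kcal/100 ml it is 125–150 ml/kg. Discharge already requires 150 ml/kg, so the extra volume on hydrolysed formula is about 2–32 ml/kg. At the slowest rate in Table 2 (12 ml/kg/day) that is at most 32/12 ≈ 2.7 days, and only where feeding is the binding criterion.

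**4. Simulation.** Inputs, all assumed except the 34-week criterion: 200,000 infants per arm, gestational age 28–34 weeks, 25 g/day gain in the NICU after day 8, 30 g/day after discharge, and discharge at the latest of 34 weeks, 1600 g and feeding readiness. Differences are hydrolysed minus control.

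| Scenario | Stay | Weight 12 weeks after discharge | Weight at postnatal day 120 |
|---|---|---|---|
| (a) Same NICU gain, feeds 5 days earlier | −2.2 days | −54 g | +11 g |
| (b) NICU gain 4 g/day slower, no feeding benefit | +0.4 days | −67 g | −80 g |

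In (a) the discharge clock creates a deficit; in (b) it hides part of one. The 1600 g gate is above the protocol's floor. Rerun at 1500 g, (a) is essentially unchanged and (b) becomes −71 g against −76 g, so the masking is then small. In both scenarios the post-discharge rate is equal by construction, so in (b) that rate alone would show no difference although the infants are lighter at the same age.

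**The case against.** **The statistical section names no time axis.** True. The schedule is a data-collection rule, and the models could use age as time scale or covariate. A condensed article may leave that to an analysis plan, so a reader should not infer that time since discharge is the model's stated axis. What stands is that the endpoint itself is defined in windows bounded by discharge and that no common-age comparison is named.

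**The endpoint is a rate.** Also true. A constant size offset does not change a slope, so the gram figures in steps 1 and 4 do not measure the error in the planned endpoint. The rate does not escape the problem, though: step 2 shows a NICU average that depends on stay, and a post-discharge rate ignores size at discharge.

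**Discharge is a natural anchor.** The study formula stops there, and one question is how infants fare on ordinary formula afterwards. That justifies keeping the discharge-anchored rates, and NICU rates are reported beside them. It does not make them sufficient for the question of unaffected growth.

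**The shift may be small.** The 34-week criterion limits early discharge, and stay is reported, so any difference would be visible. This stands as a limit on size.

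**Conclusion.** The concern holds in conditional form. The growth comparison is at risk of bias, of unknown direction and size, if stay differs between arms or if the weight and gain criteria hold back slower-growing infants. If neither happens, ages at the visits do not differ systematically and the issue is minor. The scale is about 22–30 g of attained weight per day of shift at 1500–2000 g, or in one constructed example 1.5 g/day in a NICU average rate. Both rest on assumed inputs.

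A reader might infer that the arms will certainly be compared at different ages, that the result is biased, or that no growth finding could be interpreted. The documents do not support this: they quantify no shift, the direction is open, and data for an age-based analysis are largely collected already. This is a worthwhile, cheap improvement to a secondary endpoint that carries the safety question.

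**What to change.** Leave the visits as they are and record the date of every measurement. Make the main growth-safety comparison one of attained weight, length and head circumference from birth to 3 months after discharge:

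- One repeated-measures model per measure, with postmenstrual (corrected) age as the time axis.
- Adjustment for the birth measurement, gestational age and sex.
- Group difference with 95% CI at a fixed postmenstrual age, chosen in advance and within the observed range.
- Discharge-anchored rates kept as descriptive results.

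The cost is analysis wording. Gestational age, sex and birth measurements are already collected, as are daily weights and weekly length and head circumference in the NICU. The downside is a slightly more complex model and some interpolation between visits.
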